## Abstract

Cohort studies using large-scale databases have become increasingly important in recent years. The Tokushukai Medical Group is a leading medical group in Japan that includes 71 general hospitals nationwide from Hokkaido to Okinawa, with a total of 18,000 beds, and a unified electronic medical record system. This retrospective cohort study aims to evaluate the real-world outcomes of systemic therapy for Japanese patients with cancer using this merit of scale. All adult patients with cancer who received systemic therapy using a centrally registered chemotherapy protocol system at 46 hospitals from April 2010 to March 2020 will be identified (~48,850 patients). Key exclusion criteria include active double cancer and inadequate data extraction. Data will be obtained through electronic medical records, diagnosis procedure combination data, medical prescription data, and the national cancer registration system that includes sociodemographic variables, diagnostic and laboratory tests, concomitant drug prescriptions, cost, and overall survival. Kaplan–Meier estimates will be calculated for time-to-event analyses. Stratified/conventional Cox proportional hazards regression analyses will be conducted to examine the relationships between overall survival and related factors. Our findings provide important insights for future research directions, policy initiatives, medical guidelines, and clinical decision-making.

## 1. Introduction

The first published randomized controlled trial (RCT) was conducted in 1948 to find the standard clinical treatment with streptomycin for tuberculosis [1]. Since then, RCTs have been regarded as the gold standard for addressing various clinical questions, including cancer treatment [2,3]. RCTs generally include highly selected patients with good performance status but exclude patients with complications, such as those with cardiac, renal, and hepatic diseases, and the elderly [4,5]. These conditions lead to discrepancies between the actual clinical practice and RCT outcomes. First, data on clinical outcomes and adverse events in elderly patients and patients with complications are difficult to obtain [6,7]; second, owing to low realizability, the traditional RCT design may be less suitable for emerging technologies, such as those that focus on rare genetic mutations [8]; and finally because survival data from RCTs are generally based on a very narrow observation period, and the extrapolation of the survival curve may fail to allow for the prediction of the long-term treatment effect [9].

In recent years, cohort studies using large-scale databases have become widespread. Real-world data (RWD) are defined as data related to the patients’ health status and treatment history that are collected during daily medical practice, such as data derived from electronic medical records and from hospitalization data [10]. The potential advantages of RWD are demonstrated by the limitations of the ongoing reliance on RCTs [11,12,13]. Consequently, RWD are used in various situations, such as the clinical development of drugs and post-marketing safety evaluation. The Food and Drug Administration in the United States uses RWD to expand the indications for approved drugs [14]. To facilitate the development of a rich, objective, and less biased dataset integrating a broad spectrum of evidence, protocol papers using RWD have been prepared over the past few years [15,16].

The Tokushukai Medical Group is a leading medical group in Japan that includes 71 general hospitals nationwide from Hokkaido to Okinawa, with a total of 18,000 beds, accounting for approximately 1.2% of all hospital beds in Japan [17]. The electronic medical record system that we use is unified, and medical coding of medication names and laboratory test values is standardized. This medical record system is managed by Tokushukai Information System Inc., and the patients’ medical information can be extracted from each hospital’s patient registration system. For systemic cancer therapy, a shared chemotherapy protocol system was installed in 51 hospitals by the end of March 2020. All prescribed chemotherapy regimens are approved by the regimen review committee of the Tokushukai Medical Group; therefore, the treatment schedule and dosage are unified nationwide. Among these hospitals, 46 hospitals applied the diagnosis procedure combination data (DPC), which is the Japanese claims record for acutely hospitalized patients, including information on the main diagnosis, interventions, and comorbidities. The DPC was developed as a measurement tool aimed at making acute hospital care transparent, standardizing Japanese medical care, and evaluating and improving its quality [18].

The Tokushukai REAl-world Data (TREAD) project is being developed as an observational population-based retrospective cohort study that aims to collect RWD on systemic therapy for Japanese patients with cancer in the Tokushukai Medical Group with this merit of scale.

Here, we report the main protocol of the study that will generate data through several sub-projects for each type of cancer to assess whether the results of clinical trials extend to the real world. Moreover, the data will enable the examination of temporal trends in treatment patterns, as well as treatment outcomes and prognostic factors that affect overall survival. 

## 2. Materials and Methods

### 2.1. Study Population

This study was approved by the Ethics Committee of Tokushukai Medical Group in April 2020 (no. TGE01427-024). All adult patients with cancer who received centrally registered systemic therapy at 46 DPC hospitals within the Tokushukai Medical Group from 1 April 2010 to 31 March 2020 will be identified within each of the sub-projects containing an analysis of various cancers involved in this study. The inclusion and exclusion criteria are presented in Table 1.

### 2.2. Information Source and Data Collection

Information on the patients who met the inclusion criteria will be extracted by the Tokushukai Information System Inc., while researchers will be blinded to statistical analyses. Figure 1 provides an overview of how variables will be collected.

Patient demographic data, including age, birth year and month, sex, postal code, and insurance type, were documented at the time of the issuance of medical record identification. In addition, body height, body weight, body mass index, body surface area, and date of measurement were recorded based on practical requirements. Moreover, the date of the last visit, the last date of survival confirmation, the date of death, and the diagnosis on medical receipt were automatically recorded as part of routine clinical practice. The above information can be extracted from a unified medical record system (e-Karte and Newtons2, Software Service, Inc., Osaka, Japan).

Treatment information, including inpatient and outpatient therapies, particularly chemotherapy regimens, can be retrieved from a shared chemotherapy protocol system (SSI srvApmDrop, Software Service, Inc., Tokyo, Japan). This system links the start and end date, the date of administration, the treatment interval, the number of treatment cycles, the dose of administration, the data of dose adjustment, and the performance status.

Data from the Japanese National Cancer Registry [19,20] are available for all hospitals, including the diagnosis (date, site, laterality, pathology, and differentiation), staging (clinical and pathological TNM classification [21]), date of the first visit, treatment details (surgery, endoscopic treatment, radiotherapy, chemotherapy, and endocrine therapy), and survival outcomes (last date of survival confirmation, date of death, and cause of death).

Patient, treatment, and cancer registry data are combined with anonymized identification and cleaned by Tokushukai Information System Inc. (Osaka, Japan). Patients with double cancer and/or diagnostic errors will be excluded from the study. Treatment history will be organized, and missing data will be supplemented by a direct check of medical records in cases of inconsistency or lack of information. Patients with unknown treatment history will be also excluded.

Details of hospitalization information such as diagnosis at admission (ICD-10), type of admission (scheduled or emergency), date of admission and discharge, outcome at discharge, complication (ICD-10), costs, and history of smoking (Brinkman index) can be extracted from the DPC data, which serves as the National Hospital Discharge Database for clinical studies in Japan [18,22].

Prescription data, such as the name and dose of the medicine, as well as the date and days of prescription, can be added from the electronic ordering system (e-Karte and Newtons2). The following treatment agents will be assessed in this study: (1) antitumor agents, (2) antihypertensive agents, (3) antithrombotic and antiplatelet agents, (4) antidiabetic agents, (5) antilipidemic agents, (6) antibacterial/antiviral/antifungal agents, (7) antiacid agents, (8) steroids, and (9) probiotics.

Furthermore, laboratory test information, such as blood cell count, biochemical tests, tumor markers, coagulation/fibrinogenic tests, infectious diseases, and urinalysis, can be retrieved from the electronic ordering system (e-Karte and Newtons2). The detailed parameters are listed in Table 2. Admission, prescription, and laboratory test data are combined with basic patient information with anonymized identification and cleaned again by Tokushukai Information System Inc. The final anonymized datasets, created as described above, will be handed over to statistical analysts with simplified case identification.

The analysis will be performed using statistical software (R, SAS, SPSS, or other statistical software) on computers of internal and external research institutes (Kobe University (Kobe, Japan) and deCult Co., Ltd. (Hatsukaichi, Japan)). Data will not be shared, except among computers that process and analyze them.

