### Strengths and Weaknesses

This nationwide cohort study will include a large number of patients from community-based general hospitals only, not including cancer centers or academic institutions. The cohort will comprise a certain number of patients who are unable to participate in clinical trials owing to their age, poor performance status, or complications. Therefore, this study could provide more realistic clinical data with a lower rate of loss to follow-up.

Moreover, our study will simultaneously use demographic data and treatment details, as well as the National Cancer Registry, DPC, prescription, and laboratory test data. In particular, few large-scale databases include performance status and laboratory data, which would be major considerations regarding prognostic factors. In addition, by using the DPC data, detailed information on emergency hospitalization, length of hospital stay, concomitant complications, medical costs, and outcomes can be obtained, allowing for a review of the quality and cost-effectiveness of medical care. Prescription data would be useful for evaluating drug–drug interactions. Relative dose intensity can also be computed. Individual analyses using institutional or national databases are very common; however, to the best of the authors’ knowledge, this is the first large-scale cohort study that can simultaneously handle comprehensive RWD.

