## Figures and Tables

**Figure 1 healthcare-10-02146-f001:**
[figure not shown]
Data collection overview.

**Table 1 healthcare-10-02146-t001:** Inclusion and exclusion criteria.

Inclusion Criteria
Patients with pathologically or radiologically diagnosed cancer Age ≥20 years Receiving centrally registered systemic therapy at DPC hospitals within the Tokushukai Medical Group from 1 April 2010 to 31 March 2020
Exclusion criteria
Patients who chose to opt out Simultaneous and metachronous double cancer with disease-free interval of ≤5 years, except for carcinoma in situ/intramucosal cancer cured by local treatment or endoscopic lesions diagnosed as carcinoma in situ Inadequate data extraction (e.g., missing details on past cancer treatment at other hospitals or individual patient data)

**Table 2 healthcare-10-02146-t002:** Laboratory test information.

Blood cell counts	White blood cell (WBC), red blood cell (RBC), hemoglobin (Hb), platelet (PLT), leukocyte fraction, lymphocyte (Lym), neutrophil (Neu), monocyte (Mono), eosinophil (Eo), and basophil (Baso)
Biochemical tests	Sodium (Na), potassium (K), chloride (Cl), calcium (Ca), inorganic phosphorus (IP), magnesium (Mg), aspartate aminotransferase (AST), alanine aminotransferase (ALT), lactate dehydrogenase (LDH), alkaline phosphatase (ALP), γ-glutamyl transpeptidase (GGT), total bilirubin (T-Bil), direct bilirubin (D-Bil), blood urea nitrogen (BUN), creatinine (CRE), uric acid (UA), total protein (TP), albumin (Alb), blood glucose (Glu), hemoglobin A1c (HbA1c), total cholesterol (TC), HDL cholesterol, triglyceride (TG), C-reactive protein (CRP), iron (Fe), and ferritin
Tumor markers	Squamous cell carcinoma-related antigen (SCC), cytokeratin 19 fragment (SYFRA), carcinoembryonic antigen (CEA), carbohydrate antigen 19-9 (CA19-9), carbohydrate antigen 15-3 (CA15-3), carbohydrate antigen 125 (CA125), neuron-specific enolase (NSE), pro-gastrin-releasing peptide (ProGRP), and prostate specific antigen (PSA)
Coagulation/fibrinogenic tests	Activated partial thromboplastin time (APTT), prothrombin time (PT), fibrinogen (Fib), fibrin/fibrinogen degradation product (FDP), and D-dimer
Infectious disease markers	Hepatitis B surface (HBs) antigen, HBs antibody, HB core antibody, HBe antigen, HBe antibody, HB virus DNA quantification, HC virus antibody, syphilis, and HIV
Urinalysis parameters	Urine protein qualitative, urine sugar qualitative

**Table 3 healthcare-10-02146-t003:** Sample size of each cancer type.

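### Smoking history, cost and the ICD-10 complication field have an inpatient claims record as their only named source: their hazard ratios can be biased, and the cost-effectiveness statement is not supported for total cost

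*Protocol article*

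**What the plan says.** The Introduction defines DPC by this clause: "which is the Japanese claims record for acutely hospitalized patients, including information on the main diagnosis, interventions, and comorbidities". Section 2.2 lists the DPC fields as details of hospitalization and states that "complication (ICD-10), costs, and history of smoking (Brinkman index) can be extracted from the DPC data". The article names no other source for smoking history or cost, and no other source for the coded complication field.

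The cohort is wider than the admitted population. On treatment, Section 2.2 states: "Treatment information, including inpatient and outpatient therapies, particularly chemotherapy regimens, can be retrieved from a shared chemotherapy protocol system". The entry criterion in Table 1 is "Receiving centrally registered systemic therapy at DPC hospitals within the Tokushukai Medical Group from 1 April 2010 to 31 March 2020", which asks for treatment at a DPC hospital and not for an admission.

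Two further statements depend on these fields. Section 2.5 lets models fitted on different numbers of cases be compared by average AIC and BIC per case, and a factor with p below 0.05 in the chosen model is called an important prognostic factor. Strengths and Weaknesses says that DPC supplies costs and outcomes, "allowing for a review of the quality and cost-effectiveness of medical care". The data limitations listed in that section do not mention that DPC covers admissions only.

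**The concern.** A patient treated only as an outpatient has no DPC record, and so no DPC smoking history, complication code or cost. For other patients the only record may come from an admission after therapy began, possibly because of deterioration or death. Whether the covariate is observed can then depend on the outcome.

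Three things are at stake:

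- A hazard ratio for smoking or a DPC complication could be shifted in either direction, and the p-value rule in Section 2.5 could then name the wrong factors.
- A model with smoking, fitted on patients with a DPC record, could be ranked by average AIC or BIC against a model without smoking fitted on the whole cohort. The two rest on different populations with different survival.
- Cost taken from admissions leaves out systemic therapy given to outpatients, so a regimen given mainly to outpatients would look cheaper than it is.

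**Working it through.** **Step 1. The article's own total.** Table 3: 800 + 10,000 + 10,000 + 1,000 + 5,000 + 500 + 350 + 500 + 10,000 + 1,500 + 5,000 + 2,500 + 350 + 350 + 1,000 = 48,850. This equals the total in the Abstract.

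**Step 2. Patients without a DPC record.** The number is 48,850 × (1 − a), where a is the share ever admitted. The article does not give a, so a range is assumed.

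| Assumed a | Without a DPC record |
|---|---|
| 40% | 29,310 |
| 60% | 19,540 |
| 80% | 9,770 |
| 95% | about 2,443 |

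**Step 3. Analysis restricted to patients with a record.** This is a simulated Cox model, 10 runs of n = 10,000. Assumptions: smoking prevalence 40%, true hazard ratio 1.30, baseline hazard 0.03 per month, exponential survival, uniform censoring at 12 to 60 months.

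| How the record arises | Share with record | Hazard ratio | Median survival, months |
|---|---|---|---|
| Full cohort | 1.00 | 1.297 | 20.8 |
| Baseline admission at random | 0.60 | 1.285 | 20.8 |
| Baseline admission depends on smoking only (80% v 45%) | 0.59 | 1.315 | 20.1 |
| Ever admitted: 70% of dead, 50% of living | 0.63 | 1.275 | 18.2 |
| Ever admitted: 90% and 50% | 0.77 | 1.242 | 16.6 |
| Ever admitted: 95% and 30% | 0.73 | 1.190 | 14.6 |
| Follow-up admission, 0.02 per month | 0.30 | 1.345 | 34.7 |
| Same, plus terminal admission in 80% of deaths | 0.71 | 1.256 | 16.8 |
| Follow-up admission, rate doubled in smokers | 0.37 | 1.474 | 32.8 |
| Same, plus terminal admission in 80% of deaths | 0.74 | 1.095 | 17.7 |

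Baseline records leave the estimate close to 1.30. Records from follow-up admissions move it either way and also change the survival of the analysed group.

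**Step 4. Worst case: no record coded as no complication.** Assume a complication present in 30% with no effect on survival, 50% ever admitted independently of it, and hazard doubled in the admitted. Everyone with the complication recorded is admitted, so their relative hazard is 2. Among the rest, the admitted share at the start is 0.5 × 0.7 / (0.5 × 0.7 + 0.5) = 0.35 / 0.85 = 0.412, so their relative hazard is 1 + 0.412 = 1.412. The starting ratio is 2 / 1.412 = 1.42. It rises as admitted patients in the unrecorded group die sooner, and the fitted Cox hazard ratio is 1.52 for a factor with no effect. With 30 to 70% admitted and an admission hazard ratio of 1.5 to 2.0, the result runs from about 1.2 to 1.7. At 90 to 95% admitted it is 1.04 to 1.13. In the same set-up, restriction to admitted patients gives about 1.0.

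**Step 5. Cost.** No simulation is needed. The named cost source covers admissions and the therapy under study includes outpatient treatment, so the cost of that treatment lies outside the source.

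**The case against.** A reader might infer more than the article supports.

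- **That comorbidity is known only for admitted patients.** It is not. Section 2.2 also takes from the unified record the receipt diagnosis: "the diagnosis on medical receipt were automatically recorded as part of routine clinical practice". It adds prescriptions, among them antihypertensive and antidiabetic agents, and laboratory tests. Only smoking, cost and the coded complication field rest on DPC alone.
- **That the hazard ratios are biased, or that 1.52 is the expected error.** The article never says that a missing record is coded as no complication, and steps 3 and 4 include plausible settings with almost no bias. The covariate window and missing-data rules may stand in the full protocol or analysis plan, and their absence from an article is not a fault. Section 2.5 does not name smoking or DPC complications as covariates.
- **That cost-effectiveness cannot be assessed at all.** It is neither an endpoint in Section 2.3 nor an analysis in Section 2.5. A review of inpatient cost and quality remains possible, and outpatient drug doses and dates are available from which some cost could be derived.

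All of this stands and narrows the point. Two further defences do not settle it. The direct check of medical records for missing data is described alongside treatment history and before DPC data are merged, so it does not clearly reach smoking or complications. The Table 1 exclusion for missing individual patient data, if applied to DPC fields, would remove never-admitted patients and narrow the cohort to the admitted.

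**Conclusion.** The point holds in a limited form. Three fields have an inpatient-only named source in a cohort that includes outpatients, and the stated limitations omit this. Bias in their hazard ratios is possible and can be material: 1.10 to 1.47 around a true 1.30 under the follow-up mechanisms tried. It is not established, and it is close to nil when records date from baseline and their presence does not depend on outcome given the covariates. The figure of 1.52 is an illustration that rests on a coding rule the article does not contain. Admitted share, prevalence, hazard ratios and survival parameters are all assumptions.

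The cost part is firmer because it follows from the article's own descriptions: the cost-effectiveness statement goes further than the named cost data for total cost of care. The changes are worth making because the article itself fixes the choice of source, the per-case model comparison and the cost statement.

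**What to change.** - Take baseline comorbidity from receipt diagnoses and prescriptions dated on or before the start of therapy.
- Use DPC smoking and complication fields only from admissions on or before that date. Treat an absent record as missing, never as absence of the factor. The method for handling the missing values can be left to the analysts.
- Report the share of patients with a DPC record, preferably by cancer type, and add the inpatient-only coverage to the limitations.
- Compare models with and without DPC covariates on one common case set, in place of average AIC or BIC per case.
- Restate cost as inpatient cost, and limit the cost-effectiveness statement unless a source of outpatient cost is named.

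The cost is small: wording and coding rules applied to data already planned for extraction. Receipt diagnoses are less specific than DPC codes, fewer patients will have a usable DPC smoking value, and the cost aim becomes narrower.

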### 2.3. Study Endpoints

For this study, the primary endpoint is overall survival, whereas the secondary endpoints are the time to treatment failure, recurrence-free survival, and adverse events, evaluated based on the Common Terminology Criteria for Adverse Events v.5.0 Japanese translation—Japan Clinical Oncology Group (JCOG) version (CTCAE v. 5.0-JCOG) [23].

### 2.4. Sample Size Calculation

The sample size for each cancer type is estimated based on the actual number of patients rather than specific hypotheses. Only 27 hospitals were equipped when the chemotherapy protocol system was started in April 2010, and the number of hospitals where this protocol system was used increased to 51 in March 2020. During this study period, the number of registered regimens increased rapidly, reflecting advances in oncology. These dynamic shifts preclude simple sample-size calculations. Alternatively, each sample size over the study period can be estimated based on the number of patients receiving drugs through the protocol system in 2019 (176 for biliary tract cancer, 1534 for breast cancer, 2324 for colorectal cancer, 212 for esophageal cancer, 956 for gastric cancer, 72 for kidney cancer, 1473 for lung cancer, 319 for ovarian cancer, 1026 for prostate cancer, 501 for pancreatic cancer, 71 for uterine body cancer, 83 for uterine cervix cancer, 199 for urinary tract cancer, 104 for gastrointestinal stromal tumors, and 123 for liver cancer). The expected sample sizes are listed in Table 3.

